# The influence of surface EMG-triggered multichannel electrical stimulation on sensomotoric recovery in patients with lumbar disc herniation: study protocol for a randomized controlled trial (RECO)

**DOI:** 10.1186/s13063-017-2310-z

**Published:** 2017-11-25

**Keywords:** Lumbar disc herniation, Sensomotoric deficit, Sensomotoric recovery, Electrical stimulation, Quantitative sensory testing, Lumbar sequesterectomy

## Abstract

**Background:**

Intervertebral disc degeneration is one of the most common reasons for chronic low back pain and sensomotoric deficits, often treated by lumbar sequestrectomy. Nevertheless, the prognostic factors relevant for time and quality of recovery, of the surgical procedure, relative to conservative treatment, remain controversial and require further investigation. Surface electrical stimulation (SES) may be an influential intervention, already showing positive impact on motor and sensory recovery in different patient groups. Since mechanisms of SES still remain unclear, further inquiry is needed.

**Methods/Design:**

This is a prospective, monocentric, randomized, controlled clinical trial. A total of 80 adult patients suffering from a lumbar disc herniation (LDH; 40 treated surgically, 40 conservatively) are allocated in a ratio of 1:1. Patients in the treatment group will receive surface electromyography (EMG)-triggered electrical stimulation for eight weeks, whereas patients in the control group will not obtain any additional treatment. The primary outcome parameter is defined as the cold detection threshold (CDT), determined by quantitative sensory testing (QST), 24 months after intervention. Secondary outcome parameters include the inquiry of sensory nerve function by two-point discrimination and QST, the assessment of motor nerve function by manual muscle testing, and validated scales and scores. These include: the Oswestry Disability Index (ODI) and the Core Outcome Measures Index (COMI) assessing the domains pain, back-specific function, work disability, and patient satisfaction; the EQ-5D investigating the patient’s generic health status; the painDETECT questionnaire (PD-Q) to identify neuropathic pain components; and the Beck Depression Inventory (BDI) to assess severity of depression. Moreover, neurological status, pain medication usage, and blood samples (CRP, TNFα, IL-1β, IL-6) will be evaluated. Study data generation (study site) and data storage, processing, and statistical analysis are clearly separated.

**Discussion:**

The results of the RECO study will detect the effect of EMG-triggered multichannel SES on the improvement of mechanical and thermal sensitivity and the effect on motor recovery and pain, associated with clinical and laboratory parameters. Furthermore, data comparing surgical and conservative treatment can be collected. This will hopefully allow treatment recommendations for patients with LDH accompanied by a sensomotoric deficit.

**Trial registration:**

ISRCTN, ISRCTN12741173. Registered on 15 January 2017.

**Electronic supplementary material:**

The online version of this article (doi:10.1186/s13063-017-2310-z) contains supplementary material, which is available to authorized users.

## Background

Intervertebral disc degeneration (IVDD) represents one of the most common reasons for low back pain (LBP), which is an increasing medical and socioeconomic problem in industrialized countries. Of the German population, 85% suffer from severe LBP at least once in their lifetime [28]. IVDD may present as lumbar disc herniation (LDH) that compresses a spinal nerve root and may lead to sensory and motor deficits. A surgical decompression of the spinal nerve root is often required in these cases. Lumbar sequestrectomy is the standard surgical procedure being performed in patients with radiculopathy caused by a prolapsed lumbar disc [31]. Nevertheless, a subsequent physical therapy to support the recovery of deficits may be needed.

A LDH, however, may regress over time with conservative treatment without the need for surgical intervention [26]. Several studies [3, 21, 37] have compared surgical to non-surgical treatment in patients with herniated discs, the SPORTS-Trial being widely quoted as a seminal article in this field of research [38]. Surgically and conservatively treated patients improved substantially over a period of 24 months. Due to a few limitations, conclusions on the superiority or equivalence of each treatment could not be drawn and further investigation is needed [38].

The patient’s sensory and motor recovery after a LDH, whether treated surgically or not, is influenced by various factors like gender, pain, duration, and severity of paresis [14, 22, 34]. Further parameters include: the degree of nerve root compression; functional recovery of nerve fibers; and potentially denervated muscle areas [27]. Electromyography (EMG)-triggered surface electrical stimulation (SES) is an intervention combining electrical biofeedback of muscles with neuromuscular electrical stimulation. It is known to be effective in improving weakness of paretic muscles and remodeling the function of the related nervous system [40]. SES is frequently used to further improve motor function in severe central and peripheral paresis, as muscle atrophy due to damage on the innervating nerve is prevented by active and passive stimulation of the muscle, as well as stimulation of the according nerve [2, 9, 19, 23, 30]. Previous studies not only showed a positive influence of electrical stimulation on promotion of peripheral nerve regeneration after injury in humans and animals [11, 15, 39], but also showed an increase in strength and muscle size in healthy subjects [20]. Additionally, patients with painful IVDD show elevated IL-6 and TNF-α levels not only in the IVDD itself [7, 17], but also in serum [36]. Electrical stimulation may lead to a downregulation of these pro-inflammatory cytokines [8, 33]. Nevertheless, the underlying mechanism of SES and its influence on sensomotoric recovery are still unclear and require further investigation.

So far, improvement of sensory and motor nerve function supported by SES has been infrequently subjected to well-designed clinical trials. Thus, there is a need for data with validated modern spinal outcome instruments (i.e. quantitative sensory testing [QST], objectively assessed muscle force, and patient’s self-assessment regarding satisfaction and ability). The objective of this prospective clinical trial is thus to evaluate the efficacy of EMG-triggered SES on sensomotoric recovery in patients with LDH, treated either conservatively or surgically, using validated modern spinal outcome instruments.

## Methods/Design

### Study design

The RECO-Study is a prospective, monocentric, randomized, controlled clinical trial. The study objective is to evaluate the improvement of sensory and motor nerve function in patients two years after either lumbar sequestrectomy (Population 1) or conservatively treated patients for LDH (Population 2), following the application of SES in the early stages of recovery (within two months after diagnosis or treatment decision). As the functional status, as well as sensory recovery parameters, are known to be assessed after two years of follow-up, this specific endpoint was also chosen for our study [12, 38, 41]. Randomization will be performed for application of electrical stimulation and therapy of recovery, but not for initial therapy of LDH. Outcome is assessed by QST [25], two-point discrimination testing (2PD) [32], manual muscle testing (MMT) [16], magnetic resonance imaging (MRI) parameters [18, 24], and by validated scales and scores. These include the Oswestry Disability Index (ODI) [6] and the Core Outcome Measures Index (COMI) [4] that are applied to assess the domains pain, back-specific function, work disability, and patient satisfaction. The generic health status is investigated with the EQ-5D [5]. Neuropathic pain components are identified with the painDETECT questionnaire (PD-Q) [10]. The severity of depression is assessed by the Beck Depression Inventory (BDI) [29]. Moreover, neurological status, muscle force, pain medication usage, and blood samples (CRP, TNFα, IL-1β, IL-6) [17, 35] will be evaluated. Furthermore, the timed up and go test (TUG) [13] will be performed. Primary and secondary outcome parameters are outlined in Additional file 1: Table S1.

### Trial organization, registration, and ethical aspects

Ethics approval was obtained from the committee of the Local Ethics Committee. This study complies with the World Medical Association Declaration of Helsinki Ethical Principles for Medical Research Involving Human Subjects, 2004, with Good Clinical Practice (GCP) and meets local laws and regulations including any and all applicable data privacy laws and regulations relating to the conduct of the study.

### Study population

The study protocol aims to include patients who suffer from a LDH with radiculopathy and a sensomotoric nerve dysfunction. Patients are naturally divided into two groups, whether their individual condition qualifies them for lumbar sequestrectomy according to the guidelines of DGNC and DGOOC (Population 1) or for initial conservative treatment (Population 2). If conservative treatment (including usage of pain medication according to the WHO level scheme and physiotherapy for all, and epidural steroid injection in exceptional cases, like therapy refractory radicular pain without motor deficit) is inefficient for more than six weeks, or if patients suffer from a severe paresis, surgical treatment will be performed. Population 2 is thus allowed to cross over to Population 1. Surgically treated patients will receive postoperative pain therapy according to the WHO level scheme but no additional active physiotherapy in the first eight weeks after surgery, except SES. Radiculopathy is defined as pain, paresis (muscle strength grade 4 or less), or a sensory dysfunction in a specific nerve root distribution area L3 to S1. Additionally, a radiologically determined pathology at treatment level investigated by MRI needs to correlate to the clinical symptoms. To minimize risk factors for an unfavorable outcome, patients with significant co-morbidities (see inclusion and exclusion criteria in, Additional file 2: Table S2) need to be excluded, as this may mask a difference in treatment efficacy. Informed consent is obtained from each participant.

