### Surface electrical stimulation

After a guideline-dependent decision of the initial treatment for LDH, patients will be randomized into two groups, respectively, in a 1:1 allocation ratio: 20 patients (50%) in Population 1 and 20 patients (50%) in Population 2 will receive SES, whereas the other half will follow standardized treatment algorithms adjusted to the initially chosen therapy for LDH (see Additional file 3: Figure S1).

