### Randomization

The allocation ratio within groups is 1:1 (see Additional file 3: Figure S1). The randomization code will be generated independently from the clinical investigators according to a random permuted blocks method with varying block size. Statistical Software Stata 10.0 module Ralloc version 3.5.2 (Statacorp College Station, TX, USA) will be used to generate the random code. An independent statistician will administer the randomization code.

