### Statistical analyses

All statistical analyses will be performed in consultation with the Department of Medical Statistics and Health Economics, Innsbruck Medical University, Innsbruck, Austria. Detailed descriptive statistics will be provided for the data collected and 95% confidence intervals will be calculated for all relevant estimates. The primary analysis will follow as the randomized principle. All patients with a complete pre-treatment examination will be considered for inclusion into the population. Primary outcome parameter will be the CDT. We estimate that the 24 months change of the CDT in patients treated without SES will be approximately 10%, whereas patients treated with SES should show a better improvement up to 20% of the initial threshold. In a one-way analysis of variance (ANOVA) test, group sample sizes of 35 patients in each group achieve 80% power to detect a significant difference between the CDT estimates with an estimated standard deviation of 20%. To adjust for multiple pairwise comparisons, the critical *p* value for statistical significance was adjusted to *p* ≤ 0.05. Descriptive analyses will include reporting means (with SDs) for continuous variables and frequencies (with percentages) for discrete variables. One-way analysis of variance (or non-parametric Kruskal–Wallis equivalent) will be used to assess the difference in the primary outcome of CDT between those patients that received conventional therapy (without SES) and those who received SES. Differences between each patient, compared to the not affected body site, will be analyzed using paired t-test to adjust for the clustered nature of the thresholds for each patient.

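### The primary test is an unadjusted one-way comparison that leaves out the population used in randomisation and baseline paresis, at a cost in precision

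*Protocol article*

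**What the plan says.** **Randomisation.** The section on surface electrical stimulation states: "After a guideline-dependent decision of the initial treatment for LDH, patients will be randomized into two groups, respectively, in a 1:1 allocation ratio". This gives 20 SES and 20 control patients in each population. The Randomization section repeats it ("The allocation ratio within groups is 1:1") and generates the code "according to a random permuted blocks method with varying block size". Neither section names a further stratum.

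**Primary test.** In Statistical analyses, a one-way ANOVA or its Kruskal–Wallis equivalent "will be used to assess the difference in the primary outcome of CDT between those patients that received conventional therapy" and those given SES. No covariate is named. Analysis of covariance appears only in the abbreviation list. Patients are analysed as randomised.

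**Prognostic factors.** The Background says that recovery, whether or not the patient has surgery, "is influenced by various factors like gender, pain, duration, and severity of paresis". The Study population section defines radiculopathy by pain, by paresis of strength grade 4 or less, or by sensory dysfunction. Manual muscle testing is a listed assessment in the Study design section.

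**Who is in Population 1.** Patients are divided according to "whether their individual condition qualifies them for lumbar sequestrectomy according to the guidelines of DGNC and DGOOC (Population 1"). The rest, whose first management is conservative, form Population 2. The section then says that if conservative treatment "is inefficient for more than six weeks, or if patients suffer from a severe paresis, surgical treatment will be performed". The next sentence draws the consequence: "Population 2 is thus allowed to cross over to Population 1".

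**The concern.** The trial is built in two populations that differ in initial treatment and probably in severity, and allocation is balanced within each. The stated primary test then sets that structure aside. It also leaves out severity of paresis, although the protocol itself says this matters for recovery and entry criteria let it range from none to marked.

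A one-way test puts all variation between populations and between paresis grades into the error term. The standard error is then larger than it need be, and a chance difference between arms in paresis stays in the estimate. With about 64 evaluable patients and power well below the stated 80%, precision that costs no extra patients is worth having.

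A related uncertainty concerns Population 1. The article spells out two triggers for surgery, one tied to severity of paresis and one to the duration of failed conservative care. If both kinds of patient are randomised within Population 1, the population label alone would not separate them.

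**Working it through.** **1. The plan's own figure, to set the base power.** Inputs from Sample size calculation: difference 3.4, SD 6.8 (d = 3.4/6.8 = 0.5), two-sided 0.05, power 80%.

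n per arm = 2 × (1.960 + 0.842)² × (6.8/3.4)² = 2 × 7.85 × 4 = 62.8, so 63.

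The 63 is therefore reproduced as a size per arm (126 in total). The plan uses it as a total: 63/0.8 = 78.75, rounded up to 79, which matches its 75–80. This is a separate and larger issue. Here it only fixes the starting point: 80 patients less 20% leaves 64, or 32 per arm. The two-sample t-test at 32 per arm and d = 0.5 has power 0.504.

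**2. Gain from adjustment.** Covariates that explain a share R² of the outcome variance reduce the residual SD to 6.8 × √(1 − R²), so the effective d is 0.5/√(1 − R²). The documents give no R²; the values below are assumptions. The few degrees of freedom spent on covariates are ignored.

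| Assumed R² | Power, 32 per arm | Equivalent gain in patients, 1/(1 − R²) − 1 |
|---|---|---|
| 0 | 0.504 | none |
| 0.05 | 0.524 | 5% |
| 0.10 | 0.546 | 11% |
| 0.20 | 0.595 | 25% |

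**3. Does the omission bias the test?** A simulation of 20,000 trials used 80 analysed patients, 20 v 20 within each population, and a factor present in half of Population 1 that shifts the outcome by one SD (6.8). The unadjusted test had type I error 0.043. Power for a difference of 3.4 was 0.53 unadjusted and 0.59 with population and the factor in the model. The unadjusted test is valid and slightly conservative. What it loses is power.

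**4. Chance imbalance within Population 1.** Suppose K of the 40 surgical patients carry a given prognostic feature (K is an assumption). With 20 per arm the number in one arm is hypergeometric. The probability that the arms differ by at least 4 patients (20 percentage points) is:

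- K = 8: 0.235
- K = 12: 0.301
- K = 20: 0.343

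If the feature moves 24-month CDT by 2 to 6 units (an assumption), a difference of 4 in 20 shifts the Population 1 estimate by 0.2 × 2 = 0.4 to 0.2 × 6 = 1.2 units. The primary comparison pools both populations, so the shift there is half: 0.2 to 0.6 units, or 6% to 18% of 3.4. Against a standard error of 6.8 × √(2/32) = 1.7, that is 0.12 to 0.35 standard errors.

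**5. How much could surgical indication explain alone?** A gap of 2 to 6 units between two halves of Population 1 adds variance of 2²/4 = 1 to 6²/4 = 9, against 6.8² = 46.2. That is 2% to 19% within Population 1 and about 1% to 10% over the whole trial. The upper part of the R² range in step 2 therefore needs population and paresis grade to contribute as well.

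**The case against.** The strongest objection concerns Population 1. A reader might infer from the two triggers that it mixes two opposite indications at randomisation, 20 v 20. The documents do not support that. Population 1 is defined by guideline qualification for surgery. The sentence with the two triggers leads straight into the cross-over rule, and the Discussion describes patients randomised under medical treatment who later have surgery. Patients whose conservative care fails during the trial were thus randomised in Population 2 and are analysed there. Nor are the triggers opposite: they are joined by "or", so one patient may meet both. This objection stands. What remains is that the article does not say where patients go if their conservative care failed before enrolment.

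A second inference, that the missing covariates bias the SES effect, also fails. Randomisation balances these factors in expectation, and the confidence interval already allows for chance imbalance. Finer strata are not obligatory with 40 patients per population.

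Third, the Background gives no size for the influence of paresis and no link to a thermal threshold at 24 months, so every figure for the gain is assumed. That stands too, and is why ranges are shown.

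Finally, covariates are often left to an analysis plan, which is not shown here. This has less force: the article is not silent on the primary test but commits to a one-way comparison, which leaves out even the population within which patients are randomised.

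**Conclusion.** The point holds as one of efficiency. The stated primary test leaves out population as randomised and baseline severity of paresis, although the design uses the first and the protocol calls the second prognostic. The randomised comparison stays valid, with no bias and no inflation of type I error. The loss is modest: for an assumed R² of 5% to 20%, adjustment lifts power at 32 per arm from about 50% to 52–60%, worth 5% to 25% more patients. Under the assumptions in step 4, a 20-point chance imbalance in a prognostic feature within Population 1 has a probability of roughly 24% to 34% and would move the pooled estimate by 0.2 to 0.6 units. A mixture of surgical indications within Population 1 is possible but not shown, and the conclusion does not depend on it.

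**What to change.** In Statistical analyses, replace the one-way test by a pre-specified linear model of 24-month CDT on randomised arm, with two covariates: population as randomised (surgical or conservative) and baseline paresis grade from manual muscle testing. Fix both at randomisation so that later cross-over to surgery does not change them.

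State in Study population whether patients whose conservative treatment failed before enrolment are randomised in Population 1. Add surgical indication as a covariate only if it is recorded before randomisation and both indications occur within Population 1. Otherwise that level would be nearly empty.

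The change is to analysis wording, to be made before outcome data are seen. It costs a few degrees of freedom. It needs no new assessment provided that muscle testing is done before randomisation; the visit plan, a figure not available for this review, should confirm that. Adjustment will not make up the shortfall in sample size, which needs its own correction.

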Stimulation is initially applied within three days post intervention. Patients are trained by the clinical investigator(s) at the study site to ensure proper usage of the stimulation device. Patients are then requested to perform treatment at home. Five electrodes (4 × 6.4 cm PALS latex-free neurostimulation electrodes, model 896230) are placed on the skin in the affected nerve root distribution area L3 to S1, according to instructions documented in the patient’s individual manual. For better comparability, standardized characteristic muscles for each nerve root are chosen for stimulation. M. quadriceps femoris covers distribution areas of the roots L3 and L4, M. tibialis anterior covers L5, and M. gastrocnemius is innervated by S1. Four electrodes are used to cover an as wide as possible area of each muscle, the fifth electrode is used for reference of the EMG capacity and is closely placed to bony structure (femur condyles or ankle) (see Additional file 4: Figure S2). The electrode surface of 25.6 cm^2^was chosen according to the volume of the stimulated muscles. The stimulation device (STIWELL med4, MED-EL) is started and the pre-set program (pulse width = 300 μs, frequency = 30 Hz, plateau time = 8 s, pause time = 16 s, rise time = 2 s, fall time = 2 s) is chosen. This program was developed with STIWELL specialists in the field of clinical rehabilitation and was adjusted on the condition’s special indications and expectations of recovery. The intensity will be increased until the patient feels and sees muscle contraction. If motor habituation appears, patients are instructed to increase the intensity until the comfortable tingling sensation and/or muscle contraction can be seen again. EMG triggers are imparted over the devices’ display and clearly signal the patient when to actively tense her/his muscles and when to pause. Thresholds for the EMG trigger are set at the maximum amount of electrical activity the patient is able to create. The device is set on automatic mode, which adjusts the threshold up after a successful trial or regulates it down after an unsuccessful one. Patients are instructed to perform this treatment for 1 h daily (2 × 30 min) for the following eight weeks. Time, date, and duration of each treatment should be noted in a provided document and handed out to the investigators at the next follow-up. Furthermore, treatment time, duration, and EMG thresholds can be read out directly from the device to surveil the patient’s compliance. If the treatment is conceived uncomfortable or skin irritation appears, patients are requested to immediately contact the clinical investigators.

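### SES has a different comparator in each population, yet the primary test pools both without a population term and the result is presented as one general SES effect

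*Protocol article*

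**What the plan says.** - **Background care.** Study population describes conservative care (Population 2) as "including usage of pain medication according to the WHO level scheme and physiotherapy for all". For surgical patients (Population 1) the same section provides pain therapy but "no additional active physiotherapy in the first eight weeks after surgery, except SES".
- **Intervention.** Surface electrical stimulation prescribes SES for "1 h daily (2 × 30 min) for the following eight weeks", starting within three days of the intervention. The device display is to "clearly signal the patient when to actively tense her/his muscles and when to pause", so SES includes voluntary muscle work as well as current.
- **Allocation.** The same section states that "20 patients (50%) in Population 1 and 20 patients (50%) in Population 2 will receive SES". Controls, the remaining 20 in each population, get the standard care that belongs to their initial therapy. The Randomization section repeats the 1:1 ratio within groups.
- **Primary analysis.** Statistical analyses plans a one-way ANOVA, or its Kruskal–Wallis equivalent, of the "difference in the primary outcome of CDT between those patients that received conventional therapy (without SES) and those who received SES". It names no population factor.
- **Interpretation.** The Discussion, in the abstract and in the main text, says that the results will show the effect of EMG-triggered multichannel SES and hopes for treatment recommendations for patients with LDH and a sensomotoric deficit. The main text also calls the patients well comparable because treatment is standardized. Its limitations paragraph mentions cross-over to surgery but not the difference in background care.

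**The concern.** The SES period and the period without active physiotherapy after surgery both last eight weeks. In Population 1 the trial therefore compares the SES package with no active physiotherapy. In Population 2 it compares physiotherapy plus SES with physiotherapy alone. These effects may differ, and a one-way test returns only their average.

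What is at stake is the reading of the result. A positive pooled difference could come mainly from Population 1, where the trial cannot tell SES apart from any active therapy. A null pooled difference could hide an effect in one population. In either case, a general statement about SES in LDH would go further than the two comparisons allow.

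**Working it through.** **1. The contrasts side by side**

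| | SES arm | Control arm | What the difference measures |
|---|---|---|---|
| Population 1 (surgery) | pain therapy + SES | pain therapy, no active physiotherapy for eight weeks | SES package versus no active physiotherapy |
| Population 2 (conservative) | pain medication + physiotherapy + SES | pain medication + physiotherapy | SES added to physiotherapy |

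**2. Inputs**
- Planning difference 3.4 and SD 6.8 (Sample size calculation).
- 20 patients per arm in each population (Surface electrical stimulation).
- Loss to follow-up of 20%, the upper limit given in Sample size calculation: 20 × 0.8 = 16 evaluable per cell and 32 per pooled arm.
- Assumptions made here: the SD of 6.8 applies within each population, and the Population 2 effect is r times the Population 1 effect. The article gives no value for r, so a range is shown.

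**3. The plan's own figure**

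n per arm = 2 × (1.96 + 0.84)² × (6.8/3.4)² ≈ 63. The 63 in the article reproduces as a number per arm, whereas the article uses it as a total (63/0.8 = 79, within its 75–80). That is a separate matter, and this point does not depend on it. It does explain why power is low below even when the effect is the same in both populations.

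**4. What pooling returns**

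Pooled difference = 0.5 × 3.4 + 0.5 × r × 3.4. 
Pooled SE = 6.8 × √(2/32) = 1.70. 
Power is for a two-sided 5% test, by normal approximation.

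| r | Pooled difference | Power, 32 per arm | Power, 40 per arm (no loss) |
|---|---|---|---|
| 1 | 3.40 | 0.52 | 0.61 |
| 0.5 | 2.55 | 0.32 | 0.39 |
| 0 | 1.70 | 0.17 | 0.20 |

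At r = 1 the pooled value is correct for both populations. At r = 0 the pooled 1.7 is the effect in neither.

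**5. What the separate estimates can show**
- SE per population = 6.8 × √(2/16) = 2.40, so a 95% CI is about ± 1.96 × 2.40 = ± 4.7. Power at a difference of 3.4 is 0.29 (0.35 with 20 per arm).
- SE of the SES-by-population interaction = 6.8 × √(4/16) = 3.40, so a 95% CI is about ± 1.96 × 3.40 = ± 6.7.
- Power for the interaction with 16 per cell is 0.08 at r = 0.5 and 0.17 at r = 0. With 20 per cell it is 0.09 and 0.20.

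Even the extreme split of 3.4 against 0 is only one standard error of the interaction.

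**The case against.** **The pooled result is valid.** A reader might infer that a pooled SES effect answers neither population's question. The article does not support that. Allocation is 1:1 within each population and both arms share that population's background care. The pooled difference is therefore not confounded by population. It estimates the average effect of adding SES to usual care, a coherent pragmatic question, and it equals both population effects if these agree. This part of the objection stands in full.

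**The claim concerns the package.** A reader might think the Discussion credits electrical current alone. The Background defines EMG-triggered SES as biofeedback combined with neuromuscular stimulation, and the Discussion claims an effect of that intervention. This also stands. The remaining issue is the unstated comparator.

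**The exercise contrast is easily exaggerated.** One hour daily over eight weeks is 56 h of scheduled sessions, which a reader might take as 56 h of contraction. The programmed cycle is 2 + 8 + 2 + 16 = 28 s. Contraction is then about 56 × 8/28 = 16 h (plateau only) to 56 × 12/28 = 24 h (with rise and fall). The content and amount of physiotherapy in Population 2 are not stated either, so how actively those controls exercise is unknown.

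**Subgroup estimates belong in the SAP.** An unseen SAP may well contain them, and their absence from an article would be no finding. The article, however, does name the primary test, and a one-way layout has no place for population. The Discussion foresees comparisons between initial treatments and between SES groups, but not of the SES effect across populations.

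**Separate estimates are too imprecise.** This is correct as regards confirming a difference, so they can only be descriptive. It does not argue against fitting the population term or naming the comparators.

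**Conclusion.** The point holds as a matter of analysis specification and interpretation. The primary test is not biased by pooling. The article fixes a one-way comparison that merges two different comparators, although it randomizes within the two populations, and it presents the outcome as one SES effect. In Population 1 no analysis can separate the SES package from having any active therapy, so only the wording of the conclusion can deal with that.

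The size depends on r, which the article does not give. With equal populations the pooled difference runs from 3.4 (r = 1) to 1.7 (r = 0), and power with 32 per arm from 0.52 to 0.17. This rests on SD 6.8 within each population and 20% loss.

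A reader might expect estimates by population to reveal which contrast drives the result. With standard errors of about 2.4 and 3.4 they cannot. Cross-over blurs the contrasts further: conservative treatment that is inefficient for more than six weeks leads to surgery, possibly within the eight SES weeks, which changes the background care.

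The change is worth making, but the trial remains interpretable without it.

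**What to change.** Leave care and the pooled SES comparison as planned.

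1. In Statistical analyses, replace the one-way ANOVA with a model for CDT containing SES and population as randomized. If the rank-based alternative is used, stratify it by population.
2. Report the SES effect with 95% CI for each randomized population, and the SES-by-population interaction with 95% CI. Label all three as descriptive, and state that they cannot establish which contrast drives the pooled result.
3. In the Discussion and the abstract, describe the pooled result as the average effect of adding SES to each population's usual care. Name the comparators by population as randomized: no active physiotherapy in the first eight weeks after surgery in Population 1, and physiotherapy in Population 2.
4. Add the difference in background care to the limitations, and note that cross-over to surgery may change that care.

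**Cost:** one model term, three estimates from data already being collected, and a few sentences. The downside is wide intervals by population (about ± 4.7 under the assumptions above) and a narrower headline claim.
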